### 2.3. Participants

Patients and members of the public were not formally involved in the planning or development of this study. Their contribution was indirectly integrated through insights from the literature, observations from routine clinical practice and by actively listening to patients’ opinions prior to the study, which informed the research questions and the choice of patient experience as the primary outcome. Although patients did not directly contribute to the intervention or procedures, informal feedback supported the acceptability of wearing the VR headset. Upon publication, participants will receive a summary of the findings, which will also be disseminated through institutional channels and oncology patient organisations.

### 2.4. Eligibility Criteria

Patients are eligible for inclusion if they meet all of the following criteria:confirmed oncological diagnosis;scheduled placement of a PICC or PICC-PORT as part of routine clinical care;adequate understanding of the Italian language;ability to provide written informed consent.

Patients are excluded if one or more of the following conditions are present:refusal to participate or inability to provide informed consent;cognitive, psychiatric or neurological conditions that may compromise the reliability of patient-reported outcomes or the ability to follow the basic instructions related to the procedure;significant visual or auditory impairment preventing effective use of the VR headset;sensory deficits involving the anatomical area of device insertion.

Eligible patients are recruited consecutively and enrolled according to the centralised predefined randomisation sequence.

### 2.5. Randomization and Allocation

Participants are randomly assigned to one of the two study arms in a 1:1 allocation ratio. The randomisation sequence is generated using an independent, certified web-based randomisation service (Sealed Envelope™, London, UK). Simple randomisation is employed [20], without any a priori constraint on final group size, consistent with the pragmatic, real-world nature of the trial.

According to the pragmatic approach of the study, no stratification procedures are applied. Allocation concealment is maintained through centralised, real-time assignment by the online system. After eligibility is confirmed and informed consent obtained, the treating clinician accesses the secure Sealed Envelope web interface, which reveals the allocation at the point of assignment, thereby ensuring concealment at the time of assignment and preventing foreknowledge of upcoming allocations.

Given the characteristics of the intervention, blinding is not feasible at any stage of the study. Participants are aware of whether they are receiving the VR intervention, and healthcare professionals involved in device placement are likewise aware of group allocation.

Blinding of outcome assessment is not feasible for the primary and secondary patient-reported outcomes, which are collected directly from participants aware of their allocation.

All outcomes are collected using standardised instruments applied uniformly across study arms. To mitigate the risk of bias, the operator performing the procedure is not involved in the collection of patient-reported outcomes, and objective parameters (physiological and procedural data) are extracted from clinical records by research personnel not involved in the procedure. The absence of blinding is acknowledged as an inherent methodological limitation and is considered in the interpretation of study findings.

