### 2.7. Outcomes

The primary outcome of the study is a composite patient-reported procedural experience endpoint, reflecting the overall effectiveness of the virtual reality intervention during PICC and PICC-PORT placement. Although the term “composite endpoint” is used, it refers here to a conceptual and experiential framework rather than to a statistically aggregated outcome.

This composite endpoint integrates multiple dimensions of procedural experience, including:change in procedural anxiety, which represents the prespecified principal quantitative driver of the endpoint;patient-reported comfort and satisfaction with the procedure;perceived procedural acceptability and overall tolerability.

Procedural experience is assessed immediately after completion of the procedure (T1) using structured patient-reported measures, combining ordinal rating scales and qualitative evaluation to assess complementary quantitative and experiential elements. Procedural anxiety (measured using the 10-point Visual Analogue Scale for Anxiety, VAS-A) constitutes the primary focus of analysis, while the remaining component dimensions (comfort, satisfaction and procedural tolerability) are analysed as individual, non-aggregated measures and interpreted jointly with anxiety to provide an overall understanding of procedural experience. No numerical aggregation of component scores is applied.

This approach reflects the multidimensional and subjective nature of immersive digital interventions, for which patient experience constitutes a clinically meaningful outcome.

Secondary outcomes include:procedural pain, assessed using a 10-point Visual Analogue Scale (VAS);physiological parameters, including heart rate and systolic, diastolic and mean arterial pressure as routinely monitored;procedural characteristics, including procedure duration and number of insertion attempts;qualitative assessment of patients’ perceptions and lived experiences related to the procedure, analysed using Van Kaam’s phenomenological method [18].

This exploratory analysis aims to elucidate the relationship between procedural anxiety and the other experiential dimensions and to facilitate comparison with previous studies in which anxiety was evaluated as a standalone outcome. Procedural pain and anxiety are therefore analysed separately to explore their individual contributions to the overall procedural experience.

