The planned sample size is based on a power-based rationale focusing on procedural anxiety as the principal quantitative driver of the primary composite outcome. Assuming a clinically relevant between-group difference of approximately 1.5 points on a 10-point VAS-A, a standard deviation of 2.5, a two-sided alpha level of 0.05 and 80% power, a minimum of 44 participants per group is required. To account for uncertainty in effect size estimates, anticipated variability in a real-world clinical context and potential missing data or protocol deviations, the target sample size was increased conservatively to approximately 120 participants, consistent with the trial registration.

Missing data will be handled using complete-case analysis. If the proportion of missing data exceeds 10% for any key variable, sensitivity analyses may be performed to assess the robustness of the results.

No formal multivariable adjustment is planned, in line with the exploratory and pragmatic nature of the trial and the sample size, which is powered for the anxiety-driven component of the primary outcome. Potential confounders (e.g., baseline anxiety, pharmacological therapies and clinical context) are prospectively collected to support informed interpretation of outcome variability rather than formal statistical adjustment.

The study team will perform periodic internal monitoring of data completeness and protocol adherence using REDCap audit trails.

Qualitative data will be analysed using Van Kaam’s phenomenological method [18], involving systematic coding, identification of recurring themes and synthesis of the essential meanings of patients’ lived experiences. Quantitative and qualitative findings will be integrated at the interpretation stage using a narrative approach, whereby qualitative themes are used to contextualise and deepen understanding of the quantitative results. No formal mixed-methods integration techniques (e.g., data transformation or joint displays) are planned, given the protocol focus and exploratory aims of the qualitative component. Statistical analyses will be conducted using dedicated statistical software.

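### Scheduled device (PICC or PICC-PORT) is known before allocation but is used neither in randomisation nor in the analysis: a small loss of precision that is cheap to avoid

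*Protocol article*

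**What the plan says.** All references are to the protocol article.

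- **Two devices, known in advance.** Section 2.4 makes this an inclusion criterion: "scheduled placement of a PICC or PICC-PORT as part of routine clinical care". Screening precedes randomisation, so the scheduled device is a baseline fact for every patient.
- **Randomisation.** Section 2.5: "Participants are randomly assigned to one of the two study arms in a 1:1 allocation ratio". The method is simple randomisation through a central web service, and "According to the pragmatic approach of the study, no stratification procedures are applied".
- **Analysis.** Section 2.10 names independent-samples t-tests, or non-parametric equivalents, for the between-arm comparisons, and continues: "No formal multivariable adjustment is planned, in line with the exploratory and pragmatic nature of the trial". Baseline anxiety, drug therapies and clinical context are given as examples of confounders collected to help interpretation. Device type is not among the examples.
- **Outcomes.** Anxiety on the VAS-A carries the primary inference. The secondary outcomes in section 2.7 include pain and "procedural characteristics, including procedure duration and number of insertion attempts".
- **Aim.** The Outcomes and Aim section states one overall effect in patients who receive either device. No hypothesis is stated for each device. The Introduction does sort the earlier trials by device: two with ports, one with PICC.

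**The concern.** Where a trial pools two procedures, the type of procedure is an obvious candidate for a prognostic baseline variable. Here it is binary, free to collect and fixed before allocation. Three usual ways of using it are stratified allocation, a stratified test and a covariate. The article excludes the first and, by ruling out adjustment, the others. This is a stated choice, so a statistical analysis plan that is not shown could not add device adjustment to the main comparisons without departing from the protocol.

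The reason given is that the trial is pragmatic and exploratory. That does not bear on the question, because a pragmatic trial can adjust for one known binary variable. Sample size is also mentioned, but 120 patients easily support one covariate.

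Two things are at stake. If an outcome depends on device, the device variance stays in the error term and the interval for the arm difference is wider than it need be. And if the arms happen to differ in device mix, the reader gets a narrative comment instead of an estimate that takes the difference into account.

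**Working it through.** **Step 1. Reproduce the plan's sample size.** Inputs from section 2.10: "Assuming a clinically relevant between-group difference of approximately 1.5 points on a 10-point VAS-A", and "a standard deviation of 2.5, a two-sided alpha level of 0.05 and 80% power, a minimum of 44 participants per group is required".

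n per arm = 2 (1.960 + 0.842)² × 2.5² / 1.5² = 2 × 7.85 × 2.778 = 43.6, rounded up to 44. The stated figure reproduces by the normal approximation (the exact t-test gives 44.6, hence 45).

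Section 2.10 then says "the target sample size was increased conservatively to approximately 120 participants". At 60 per arm the standard error (SE) of the arm difference is 2.5 × √(2/60) = 0.456. Power is Φ(1.5/0.456 − 1.96) = 0.908, or 0.903 by the t-test.

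**Step 2. Chance imbalance in device mix.** Let p be the PICC-PORT share (an assumption; the article gives none). With 60 per arm, the between-arm difference in share has SD √(2p(1−p)/60).

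| p | SD (points) | 95% within (points) | P(>10 points) | P(>15 points) |
|---|---|---|---|---|
| 20% | 7.3 | ±14.3 | 17% | 4% |
| 30% | 8.4 | ±16.4 | 23% | 7% |
| 50% | 9.1 | ±17.9 | 27% | 10% |

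A simulation of simple randomisation of 120 patients, counting differences of 10 points or more, gives 23%, 28% and 23% at shares of 30%, 50% and 70%.

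**Step 3. Consequence for VAS-A.** Let g be the mean difference between devices on the analysed VAS-A outcome (assumed 0.5-1.5 points), with the total SD held at 2.5.

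- Shift in the arm difference = g × imbalance. At p = 20-50%, 95% of shifts lie within a limit that runs from 1.96 × 0.5 × 0.073 = 0.07 to 1.96 × 1.5 × 0.091 = 0.27 points. Compare the SE of 0.456 and the target difference of 1.5.
- Residual variance after adjustment = 6.25 − g²p(1−p). In the most favourable case (g = 1.5, p = 0.5) this is 6.25 − 0.5625 = 5.69, and power rises from 0.908 to 0.931. In the least favourable case (g = 0.5, p = 0.2) it rises to 0.909.
- Simulation with 10,000 runs per scenario and simple randomisation:

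| p, g | Type I error, unadjusted / adjusted | Power, unadjusted / adjusted |
|---|---|---|
| 30%, 1.0 | 0.047 / 0.047 | 0.900 / 0.904 |
| 50%, 1.5 | 0.050 / 0.050 | 0.899 / 0.919 |

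**Step 4. Consequence for procedure duration.** Assumed, not in the article: the devices differ by d = 10 or 20 min, the within-device SD is 10 min, and p = 50%.

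- Variance ratio without adjustment = 1 + p(1−p)d²/SD² = 1 + 0.25 × 100/100 = 1.25, or 1 + 0.25 × 400/100 = 2.0. The SE is therefore larger by a factor of √1.25 = 1.12 to √2 = 1.41.
- SE at 60 per arm: 10 × √(2/60) = 1.83 min with device in the model, and 2.04 to 2.58 min without it.
- A 10-point imbalance moves the arm difference by 0.10 × 10 = 1 min to 0.10 × 20 = 2 min, which is about 0.5 to 0.8 of the unadjusted SE.

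**Step 5. What device-specific results could show.** At a true difference of 1.5 points with SD 2.5, power within one device is 0.31 (the smaller group at a 20% share) to 0.64 (50% share). An interaction of 1.5 points has power 0.26-0.38, and its 95% interval has a half-width of 1.8-2.2 points. Results by device can be described but not tested usefully.

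**The case against.** The strongest reply is that nothing is invalid here. Chance imbalance under randomisation is sampling variation, and the unadjusted standard error already contains it. Imbalance and extra variance are one cost and must not be counted twice. A reader might infer that a device imbalance produces a false or biased arm difference. The simulated type I error, near 5% with and without adjustment, does not support that.

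A reader might also infer that a claim for each device goes untested. The article makes no such claim: its aim is one effect in the recruited mix, and that is tested. Only consistency across devices is left unexamined, and reporting by device is commonly left to an analysis plan that is not shown.

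Other points on this side also stand:

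- The main comparison is of changes in VAS-A, so a device difference that is present at baseline and persists is already subtracted.
- No document figure shows that any outcome depends on device. The Introduction sorts earlier trials by device without saying that anxiety, pain or duration differ.
- Duration is a secondary outcome. The remarks about unprolonged procedures describe earlier studies and are not a hypothesis of this trial.
- Simple randomisation is the least predictable scheme, which has value in an unblinded single-centre trial where the treating clinician obtains each allocation. Blocks within device strata would give up some of that, so the lack of stratification is defensible in itself.

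One thing is left unanswered: with allocation unstratified, why should the analysis also ignore a variable that is known before randomisation and costs nothing?

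**Conclusion.** The point holds as a cheap improvement of minor severity. It is not a threat to validity. The pooled comparison is unbiased and keeps its error rate.

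For VAS-A the gain from adjustment runs from negligible to about 2 points of power, on a base of about 90%, for assumed device effects of 0.5-1.5 points and PICC-PORT shares of 20-50%. For procedure duration the gain could matter more: a standard error larger by 12-41% than it need be, if the devices differ by 10-20 min with a within-device SD of 10 min. If the devices do not differ on an outcome, there is essentially nothing to gain for that outcome. All these sizes rest on assumed device mixes and device effects. The imbalance probabilities need only the assumed mix.

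**What to change.** Leave the randomisation as it is and amend section 2.10:

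1. Replace the blanket exclusion of adjustment with a prespecified rule: scheduled device (PICC / PICC-PORT) is a covariate in the between-arm models for VAS-A, pain and procedure duration, and in a suitable model for number of attempts. Where a rank test is used, use a version stratified by device. Use the scheduled device, because it is fixed before allocation.
2. Report the arm difference with its confidence interval separately for each device, labelled descriptive, without device-specific significance claims.
3. State the enrolled device mix, overall and by arm, and word the conclusion for that mix. If one device dominates, say so.

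The change should be dated before the outcome data are examined by arm. It is available whether or not recruitment has started.

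Cost: one baseline field already known at screening, one degree of freedom, and slightly more analysis work. The device-specific intervals will be wide and must be presented as such.

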### 2.10. Data Management Plan and Analysis

Study data will be entered into an electronic database in REDCap, used exclusively for data management and not for randomisation. All entered data will be pseudonymised, and access will be restricted to personnel specifically authorised for the study through dedicated password-protected accounts. The data will be stored on an institutional server of the study hospital and retained according to the relevant regulations. Identifiable information will be kept separate from research data, ensuring full confidentiality.

De-identified individual participant data, the data dictionary and the statistical code will be made available upon reasonable request to the Principal Investigator. No identifying information will be shared.

Given the minimal-risk nature of the study and its single-centre design, no formal monitoring of trial conduct is planned. The research team will oversee the study, protocol adherence and data collection as part of routine clinical practice.

All analyses will be conducted according to the intention-to-treat (ITT) principle. Descriptive statistics will be used to summarise participants’ demographic and clinical characteristics. Continuous variables will be reported as means and standard deviations or medians and interquartile ranges, as appropriate, according to variable distribution, while categorical variables will be presented as frequencies and percentages.

For the primary composite outcome, between-group comparisons will focus on procedural anxiety (VAS-A) as the prespecified principal quantitative driver of the composite endpoint. Independent samples Student’s *t*-tests, or non-parametric equivalents when appropriate, will be used for between-group analyses. Patient-reported comfort, satisfaction and procedural tolerability will be analysed as individual, non-aggregated component dimensions of the composite endpoint using appropriate parametric or non-parametric methods and interpreted jointly with anxiety. Secondary quantitative outcomes, including procedural pain and physiological parameters, will be analysed using similar inferential methods.

Within-group pre- and post-procedural comparisons will be explored using paired statistical tests. Statistical significance will be set at a two-sided *p* < 0.05.

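### The protocol rules out blinding at every stage, but its reasons do not reach the quantitative analysis, which can be done on coded arms with one test fixed in advance

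*Protocol article*

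**What the plan says.** Section 2.5 (Randomization and Allocation) attributes the lack of blinding to the characteristics of the intervention and concludes that "blinding is not feasible at any stage of the study". It then gives its reasons. Participants know whether they wear the headset, and "healthcare professionals involved in device placement are likewise aware of group allocation". It adds: "Blinding of outcome assessment is not feasible for the primary and secondary patient-reported outcomes". Physiological and procedural data are handled differently, being "extracted from clinical records by research personnel not involved in the procedure". The analyst is not mentioned.

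Section 2.10 (Data Management Plan and Analysis) describes a pseudonymised REDCap database, "used exclusively for data management and not for randomisation". For anxiety it names Student's t-test, "or non-parametric equivalents when appropriate, will be used for between-group analyses". Comfort, satisfaction and tolerability are to be analysed "using appropriate parametric or non-parametric methods and interpreted jointly with anxiety". Complete-case analysis is the fixed rule for missing data. Above 10% missing on a key variable, "sensitivity analyses may be performed to assess the robustness of the results".

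The Outcomes and Aim section makes the between-group comparison of changes in VAS-A the main statistical analysis. Section 2.7 likewise lists change in anxiety as the principal quantitative component.

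**The concern.** Patients and operators plainly cannot be blinded to a headset, and a patient rating their own anxiety is an unblinded assessor. That argument does not extend to someone running a two-sample comparison on a data file. By covering every stage, the sentence gives up masking of the quantitative analysis without a reason. An analysis plan that introduced it would contradict the protocol.

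This matters here because the outcomes are subjective and the trial is open-label, and because some decisions are left until the data are in hand. These are the choice between a t-test and a rank test, the methods for the other three domains, and how four separately analysed domains are read together. An analyst who knows the arms can make these choices knowing which way they push the result.

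**Working it through.** **1. Scope of the statement against scope of the reasons**

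| Stage | Reason given in Section 2.5? | Masking feasible on the text? |
|---|---|---|
| Participants | Yes | No |
| Staff placing the device | Yes | No |
| Assessment of patient-reported outcomes | Yes | No |
| Extraction of physiological and procedural data | None; done by staff outside the procedure | Not claimed, not excluded |
| Quantitative analysis | None | Yes: allocation is generated outside REDCap, so a coded file looks practicable |
| Qualitative analysis | None | No: answers about the experience are likely to reveal the arm |

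The statement is wider than its reasons, most clearly for the quantitative analysis.

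**2. The plan's own sample size**

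Inputs from Section 2.10: difference 1.5, SD 2.5, two-sided alpha 0.05, power 80%.

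n per arm = 2 × (1.960 + 0.842)² × 2.5² / 1.5² = 2 × 7.85 × 2.778 ≈ 43.6, rounded up to 44.

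This reproduces the stated 44 per group. The t-based calculation gives 44.6, or 45. At 60 per arm (half of 120), power is about 0.90–0.91. Nothing in this point changes these figures.

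**3. How far an open choice of test can move the type I error**

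Null simulation: 20,000 trials per scenario, 60 per arm, integer scores from 0 to 10, same distribution in both arms, outcome = change from T0 to T1. Two score shapes were used: roughly normal with SD 2.5, and right-skewed. The T0–T1 correlation was 0.3, 0.5 or 0.7. Shapes and correlations are assumptions, since the document gives neither. The Monte Carlo standard error is about √(0.05 × 0.95 / 20,000) = 0.15 percentage points.

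| Shape | Correlation | t-test alone | Mann-Whitney alone | Smaller p of the two |
|---|---|---|---|---|
| Roughly normal | 0.3 | 5.1% | 4.8% | 5.8% |
| Roughly normal | 0.5 | 5.1% | 5.0% | 5.9% |
| Roughly normal | 0.7 | 5.0% | 4.9% | 5.9% |
| Skewed | 0.3 | 5.0% | 5.1% | 6.7% |
| Skewed | 0.5 | 5.0% | 5.1% | 6.7% |
| Skewed | 0.7 | 4.8% | 4.8% | 6.6% |

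Either test, fixed in advance, holds its level. Always reporting the smaller p gives 5.8–6.7% here. Separate simulations gave 5.3–6.4% and 5.7–6.6%, so about 5–7% is a fair summary.

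**4. What masking does and does not do**

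Swapping the labels A and B leaves a two-sided t-test or Mann-Whitney p-value unchanged. A masked analyst could still pick the smaller p, so the excess in step 3 is removed by fixing the test, not by coding the arms. What coding hides is direction: which arm looks better on each domain when choices about reporting and joint interpretation are made.

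**The case against.** The strongest reply is that the sentence is loose wording. It opens with the nature of the intervention, and the text after it speaks only of patients, staff and patient-reported assessment. The authors may never have considered the analyst. Moreover, a journal article condenses the full protocol, and the criterion for choosing a test, the sensitivity method and analyst masking are commonly settled in an analysis plan that is not shown. The second part stands: the absence of those details is not the point here. The first part narrows the point to a correction of wording but does not remove it, because the document states a rule that is too broad.

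Three stronger readings are tempting, and the documents do not support them.

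- A reader might infer that change versus post-procedure VAS-A is also open, making four analyses to choose from. In the same simulation, the best of those four gives about 10–12.5%. But the Outcomes and Aim section fixes the comparison of changes as the main analysis, and Section 2.7 agrees. The shorter wording in Section 2.10 names no competing analysis, so that figure does not describe this plan.
- A reader might infer that optional sensitivity analyses can move the primary p-value. They cannot, because complete-case analysis is fixed as the rule. They can only affect what is reported in support.
- A reader might infer that the person collecting T1 data could usefully be masked. The rater is the unblinded patient, and open questions about the experience are asked at the same visit, so the arm would probably come out. Section 2.5 already keeps the operator away from patient-reported outcomes.

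Patient-level unblinding also remains the larger source of bias. Section 2.5 and the Discussion acknowledge it.

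**Conclusion.** The point holds in limited form. The claim that no stage can be blinded is wrong for the quantitative analysis, and nothing in the article stands in the way of coded arms. The measurable consequence is small: at most about two percentage points of type I error above 5%, and only if the more favourable of two tests on change is always reported. That size rests on assumed score shapes and correlations and on 60 per arm, which simple randomisation will only approximate. The benefit of masking itself is real but was not quantified. It lies in keeping direction out of the reporting and joint-interpretation choices, and it works only alongside a test fixed in advance.

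**What to change.** Replace the sentence in Section 2.5 with wording such as:

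> Participants, operators and the assessment of patient-reported outcomes are not blinded. The quantitative analysis is carried out on a dataset with arms coded A/B. The primary test for change in VAS-A (one named test), the handling of missing data and the analysis code are locked before the key is released.

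Name the single primary test in Section 2.10 to match.

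The cost is small. Someone already on the team must prepare the coded export and hold the key. No extra patients or visits are needed. The qualitative answers cannot be masked, so they should be kept out of the coded file until the quantitative analysis is locked.
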